#### Data collection process

After obtaining permission from Isfahan University of Medical Sciences, the researchers will select the participants by referring to research environments. In the qualitative phase, data collection methods include individual, in-depth, open, and semi-structured interviews along with focus group discussions and field noting. The interviews will be recorded. After explaining objectives and methodology of the study, the researcher will receive written consent regarding participation in the research, further interviews, and recording the interviews. Location of the interviews will be selected by the participants. If a person does not agree with recording, the researcher should try to create a friendly relationship and convince the person to consent to the recording procedure. In the next step, the cause of concern will be examined. If the participant’s concern is due to confidentiality, the researcher will try to convince him/her that confidentiality is fully respected. Finally, if the participant insists on this decision, the interview should not be recorded, but noting is allowed.

In semi-structured individual interviews, the first interviews are done with the aim of understanding possible and unpredictable issues. The general questions of semi-structured interviews are identified based on the resulted information. At the end of each interview, the narrative will be transcribed immediately, and data analysis will be done simultaneously with data collection. Data collection continues until saturation - as long as no new code or data is extracted. At this point, data saturation and adequacy will be verified.

#### Data analysis

A conventional content analysis method, introduced by Graneheim & Lundman (2004), is used for data analysis. Each interview will be transcribed immediately at the end of recording. After extracting the general idea, the narrative will be analyzed line by line, and its meaning units will be identified. Compact meaning units and codes will be extracted from these meaning units. After extracting the primary code, the data will be reduced and divided into sub- categories and main categories, based on their appearance [30].

#### Rigor and trustworthiness

For reliability and validity analysis, four criteria are suggested: credibility, dependability, transferability, and confirmability [31]. Different measures will be taken into consideration in order to improve credibility of this study, such as selecting the participants with maximum variety, spending sufficient amount of time on data collection, performing in-depth interviews in different locations and times, and mixing multiple data collection methods including individual interviews, focus group discussions, and field noting. For verification of extracted codes and data or their modification, they will be reviewed by the participants.

For confirming the reliability of the findings, some examples of code extraction methods and their corresponding interview narratives will be reviewed by an external supervisor in order to control the accuracy of researcher’s perception and to find contradictory cases. For increasing transferability, study findings will be presented to people who have similar characteristics with the participants in order to compare the results of this study with their own experiences.

Regarding verification, the researcher will explain the whole procedure, including recording, transcription, code extraction, and categorization. In order to verify the coding procedure, some of the research colleagues and faculty members, who are acquainted with qualitative research analysis and do not want to participate in this research, are asked to review the procedure.

### Second phase: designing the intervention program

After collecting the required data by qualitative study, the second phase of the study starts. The purpose of this phase is designing an intervention program for sexual health care of educable intellectually disabled adolescent girls. In this phase, the required strategies are extracted based on the results of qualitative phase and a literature review of papers and texts. These strategies will be validated by expert panel. Narrative review method is used for analyzing interview narrative which include electronic search in the area of the study. Moreover, the researcher will have access to library resources (reference books and dissertations) to obtain further information. Multiple databases are available for searching the related papers, such as Scopus, MEDLINE, Ovid, ProQuest, Cochrane Library, Science Direct, Web of Science, PubMed, Embase, Magiran, SID, Google Scholar, and CINAHL.

In this phase, all the English and Persian qualitative, quantitative, and mixed methods studies on educable intellectually disabled adolescent girls, sexual problems, sexual health of educable intellectually disabled adolescent girls, sexual health promotion, and adolescent sexual health care interventions, which have been published during 2006 to 2018, will be studied and analyzed. In the next phases, search will be narrowed down to specific mixed keywords, including educable intellectually disabled and “sexual health”, educable intellectually disabled and “sexual problems”, educable intellectually disabled and “sexual health needs”, educable intellectually disabled and “changes in puberty”, educable intellectually disabled and “sexual experience”, educable intellectually disabled and “sexual understanding”, educable intellectually disabled and “sexual health promotion”, educable intellectually disabled and “elimination of sexual problems”, educable intellectually disabled and “risk management”.

#### Holding a panel of experts

The objectives of this phase is to extract relevant strategies of sexual health care of adolescent girls from qualitative study and analyze the interview narratives in expert panel in order to prioritize their function. Then, the suitable intervention program will be selected and executed in the quantitative phase based on this prioritization. For this end, a decision making matrix will be extracted for prioritization of the extracted strategies from qualitative study and literature review of papers and texts. In this matrix, each strategy is provided with a score from 1 to 3 based on three criteria of costs, ease of execution, and time. This matrix will be sent for some specialists in the Delphi Round 1, average score will be calculated for each solution, high priority strategies will be identified, and consequently, a suitable intervention method will be selected. In Delphi Round 2, the selected intervention method will be evaluated qualitatively in a meeting with the presence of research team and panel members (psychiatric specialists, psychologists, gynecologists, reproductive health professionals, midwives, teachers, mentors, and authorities of The Ministries of Health and Welfare and The Ministries of Education). A copy of the intervention program will be presented to the experts who will be returned to the researcher at the end of the meeting. Comments and suggestions will be collected and applied in order to finalize and execute the program in the third phase (quantitative study).

### Third phase: quantitative study

#### Type of quantitative study

Quantitative phase of the study will be carried out using a three-group clinical trial.

#### Research population

The targeted populations for quantitative study are all the mothers of educable intellectually disabled adolescent girls who have referred to rehabilitation centers covered by The Ministry of Health and Welfare, and professional and pre-professional secondary schools covered by Special Education Organization of Isfahan.

#### Research sample

Study sample includes mothers of educable intellectually disabled adolescent girls who will be selected by convenience sampling and have all the inclusion criteria.

#### Research environment

This study will be carried out in three Girl’s Rehabilitation Centers covered by The Ministry of Health and Welfare, two professional secondary schools, and one pre-professional secondary school covered by The Ministry of Education in Isfahan. The reason for selecting such kind of environment is easy access to mothers of educable intellectually disabled adolescent girls and characteristics of the research unit.

#### Sample size

Sample size will be 27 participants in each group considering 95% confidence interval, 80% trial power, d = 2.9 for awareness, d = 11.3 for attitude, d = 5 for mothers’ self-efficacy, and 10% loss.

#### Sampling method

This clinical trial has two intervention groups and one control group. After identifying the centers covered by The Ministry of Health and Welfare and professional and pre-professional secondary exceptional schools, three rehabilitation centers covered by The Ministry of Health and Welfare and three exceptional secondary schools (two professional secondary schools and one pre-professional secondary school) will be selected non-randomly. Among these six centers and based on ALLOCATION and RANDOM software, one exceptional school and one rehabilitation center covered by The Ministry of Health and Welfare will be selected for each of the intervention group 1, intervention group 2, and the control group. Afterwards, the mothers with inclusion criteria will be selected from each center via convenience sampling method.

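### Centers are allocated within site type, but the number of mothers is fixed only per arm and the stated comparison does not name site type, so an unadjusted arm difference can carry a school/rehabilitation difference

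*Protocol article*

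**What the plan says.** All references are to the third (quantitative) phase of the protocol article.

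- **Sampling method, arms:** "This clinical trial has two intervention groups and one control group".
- **Sampling method, allocation:** six centers, three rehabilitation centers and three schools, are chosen non-randomly. Software then assigns them so that "one exceptional school and one rehabilitation center covered by The Ministry of Health and Welfare will be selected for each of the intervention group 1", and likewise for the other two arms. Two of the schools are professional and one is pre-professional.
- **Sampling method, mothers:** after the centers are assigned, "the mothers with inclusion criteria will be selected from each center via convenience sampling method". The implementation section repeats this: mothers are telephoned, and those willing and eligible are enrolled by convenience.
- **Sample size:** "Sample size will be 27 participants in each group". The target is per arm; no number or share per center is given.
- **Implementation:** all three questionnaires are completed before the intervention, immediately after it and one month later, so baseline scores will exist.
- **Data analysis:** a list of unadjusted tests (among them ANOVA and Mann-Whitney), then ANCOVA to adjust for variables that are not named. Site type is not mentioned.

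**The concern.** Giving each arm one school and one rehabilitation center ensures that both site types are present in every arm. It does not ensure that they carry the same weight. An arm can reach 27 with mostly school mothers while another reaches 27 with mostly rehabilitation mothers, depending on how large each center is and how easily its mothers are reached.

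The two groups of mothers may differ in awareness, attitude or self-efficacy, or in what their center already provides. If they do and the mix differs by arm, a comparison that ignores site type attributes part of that difference to the intervention. This does not require selective consent or a recruiter who knows the allocation; an unequal mix is enough.

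**Working it through.** **1. The planned sample size and what it can detect.** The article gives "Sample size will be 27 participants in each group", "considering 95% confidence interval", "80% trial power", 10% loss, and differences of "d = 2.9 for awareness, d = 11.3 for attitude, d = 5 for mothers’ self-efficacy". No SD is stated, so 27 can be neither reproduced nor refuted. It can be read backwards, assuming a two-sided 5% test:

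- 24 / (1 − 0.10) = 26.7, rounded up to 27, so 27 is consistent with 24 evaluable mothers per arm.
- Normal approximation: (1.96 + 0.84) × √(2/24) = 0.81 SD detectable.
- Exact t-test with 24 per arm: 0.826 SD detectable.

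The value 0.826 SD serves as the yardstick below.

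**2. Spurious difference from unequal mix.** For two arms with school shares p1 and p2, and a school-versus-rehabilitation gap of D (in SD units), an unadjusted comparison is shifted by

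shift = (p1 − p2) × D.

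The article gives neither the shares nor D. Both are assumptions here.

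*Illustration with clearly unequal splits, 20:7 against 10:17.* p1 − p2 = (20 − 10)/27 = 0.370.

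| Assumed D (SD) | Shift (SD) | Share of 0.826 SD | Rejection rate of a nominal 5% t-test, 24 per arm, no intervention effect |
|---|---|---|---|
| 0.3 | 0.370 × 0.3 = 0.11 | 13% | 6.6% |
| 0.5 | 0.370 × 0.5 = 0.19 | 22% | 9.6% |
| 0.8 | 0.370 × 0.8 = 0.30 | 36% | 17.1% |

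*Near-equal splits, 14:13 against 13:14.* p1 − p2 = 1/27 = 0.037. For D = 0.3, 0.5 and 0.8 the shift is 0.01, 0.02 and 0.03 SD, and the rejection rate stays at about 5%.

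*More extreme splits, 20:7 against 7:20.* p1 − p2 = 13/27 = 0.481. For D = 0.5 and 0.8 the shift is 0.24 and 0.39 SD.

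**3. What the rejection rates mean.** They apply to a post-intervention comparison with no adjustment for baseline or site type. They also treat mothers as independent within centers. With whole centers allocated, two per arm, an individual-level test need not hold 5% even with identical splits. The rates therefore isolate the mix component and do not predict the trial's actual error rate.

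**4. What the fix does.** With equal shares, p1 − p2 = 0 and the shift is 0 for any D. With unequal shares, site type can still be adjusted for, because both types occur in every arm. With 3 × 24 = 72 evaluable mothers, a three-arm comparison has 72 − 3 = 69 residual degrees of freedom. Adding site type leaves 68, and adding the baseline score leaves 67.

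**The case against.** The strongest reply has four parts.

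- **Silence is not a rule.** The article says how mothers are chosen within a center; it does not say that the number per center is free. A condensed article may leave a per-center target to the full protocol. This stands. A reader might infer that the plan deliberately leaves the split to convenience, or that the arms will be unbalanced. The text supports only that the number is fixed per arm and that no split is stated. Likewise, that the one-plus-one allocation was meant to balance site type is an inference; no such aim is stated.
- **ANCOVA is planned and could include site type.** This also stands: a reader might infer that the analysis leaves site type out, but the covariates are unnamed, so the text cannot show that. It remains true that the stated comparison does not name the factor within which the centers were allocated, and that unadjusted tests are listed beside the ANCOVA.
- **Baseline scores are collected.** A stable level difference between site types would appear at baseline and be reduced by baseline adjustment or change scores. This stands and makes the figures above an upper illustration. It does not remove differences in how scores change, for example if centers differ in what they provide during follow-up.
- **The size rests on assumed splits and an assumed gap.** This is correct, which is why a range is shown, including splits at which the effect is negligible.

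**Conclusion.** The point holds in a conditional form. Centers are allocated within site type, the number of mothers is set only per arm, and site type is not named in the stated comparison. An unadjusted comparison is therefore open to a site-type difference if two things are both true: the mix differs between arms, and the two kinds of mothers differ on the outcome. Under the illustrative splits of 20:7 and 10:17 and an assumed gap of 0.3 to 0.8 SD, the spurious difference is 0.11 to 0.30 SD; with near-equal splits it is 0.03 SD or less.

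A reader might take from the table that the trial's false-positive rate is about 10%. The documents do not support that. They give neither center sizes nor a site-type gap, and the figure presumes that the baseline scores go unused.

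The point is modest in size, and cheap to settle before recruitment. It is separate from, and smaller than, the problem of having only two centers per arm.

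**What to change.** 1. **Analysis.** State that the between-arm comparison is an ANCOVA with arm and site type (school or rehabilitation center) as factors and the baseline score of the same questionnaire as covariate. This analyses the trial by the strata within which centers are allocated.
2. **Recruitment.** Add a target of about the same split in every arm, for example 14 mothers from one site type and 13 from the other, the same way round in each arm, keeping 27 per arm. If a center falls short, fill the arm from its other center and rely on the site-type factor. Do not shrink all arms to match the smallest center, because that would take arms below 27 and cost power.
3. **Reporting.** Give the number of mothers per center in each arm.

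**Cost:** a sentence in each of the two sections, one degree of freedom for site type (plus one for the baseline score), and possibly slower recruitment.

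**What it leaves open:** center effects with only two centers per arm, and the fact that one arm must receive the only pre-professional school. Neither is corrected by a site-type factor or an equal split.

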#### Data analysis

The collected data will be analyzed by descriptive statistical methods (mean, standard deviation, minimum, and maximum), inferential statistics (paired t-test, Chi-squared test, Fishers exact test, ANOVA, Wilcoxon test, and Mann-Whitney test), and SPSS v20 software. ANCOVA will be used for adjusting intervening variables.

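### Six centers, two per arm, are randomised, but the sample size and the listed tests treat mothers as independent, so the stated 80% power and 95% confidence are not properties of this design

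*Protocol article*

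**What the plan says.** All of this is in the protocol article, under the third (quantitative) phase.

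- **Sampling method.** "This clinical trial has two intervention groups and one control group". Three schools and three rehabilitation centers "will be selected non-randomly". The allocation step is then applied to them: "Among these six centers and based on ALLOCATION and RANDOM software". As a result, every arm gets two whole centers, one of either type: "one exceptional school and one rehabilitation center covered by The Ministry of Health and Welfare will be selected for each" arm. Mothers come last: "Afterwards, the mothers with inclusion criteria will be selected from each center via convenience sampling method".
- **Sample size.** "Sample size will be 27 participants in each group considering 95% confidence interval, 80% trial power". The other inputs are a difference for each of awareness, attitude and self-efficacy, and 10% loss. No standard deviation, ICC, design effect or number of clusters is among them.
- **Data analysis.** The listed methods are descriptive statistics, "inferential statistics (paired t-test, Chi-squared test, Fishers exact test, ANOVA, Wilcoxon test, and Mann-Whitney test"), and ANCOVA for intervening variables that are not named. Center does not appear in any of them.

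**The concern.** The unit that receives an arm is the center. No mother is randomised, so this is a cluster-randomised trial with two clusters per arm, although the article calls it only a three-group clinical trial. The sample size and the between-group tests belong to a different design, in which each mother is an independent unit.

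Mothers from the same center may have correlated scores. If they do, mother-level standard errors are too small, the tests reject too often when there is no effect, and a difference between particular centers can be read as a program effect. The stakes are set by the Discussion, which says that a program that works could become a leading guideline for this population.

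This is not detail left to a fuller document. The article itself states the allocation, the sample-size inputs and the tests, and they do not fit together.

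**Working it through.** **Inputs.** From the article: 3 arms, 6 centers, 2 per arm, 27 mothers per arm, 95% confidence, 80% power, 10% loss. Assumed: two-sided alpha of 0.05, equal numbers per center, a single post-intervention score, and an ICC (ρ), which the article does not give and which is therefore shown over a range.

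**1. The plan's own figure.** Without a standard deviation, 27 cannot be derived from the stated differences. It can only be back-solved: 24 / (1 − 0.10) = 26.7, rounded up to 27. So 27 is consistent with 24 evaluable mothers per arm and no design effect. The difference detectable with 24 independent mothers per arm at 80% power is

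- normal approximation: (1.960 + 0.842) / √(24/2) = 0.81 SD;
- t-test with 46 df: 0.83 SD (0.826), used below.

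**2. Design effect.** With 24 / 2 = 12 mothers per center, DE = 1 + (12 − 1)ρ. This gives 1.22, 1.55 and 2.10 at ρ = 0.02, 0.05 and 0.10.

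**3. Type I error of the planned mother-level tests.** For two groups, the approximation is 2 × [1 − Φ(1.96 / √DE)]. The t-test and ANOVA columns are from 20,000 simulated trials of 3 arms × 2 centers × 12 mothers with no effect.

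| Assumed ICC | Formula, two groups | Simulated t-test | Simulated three-arm ANOVA |
|---|---|---|---|
| 0 | 5.0% | 4.8% | 4.8% |
| 0.02 | 7.6% | 7.7% | 8.6% |
| 0.05 | 11.5% | 11.4% | 14.3% |
| 0.10 | 17.6% | 18.4% | 25.2% |

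A repeat with 40,000 trials agreed to within one percentage point.

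**4. Power of an analysis of center means.** Six means less three arms leave 3 error df (critical t 3.182). Adding center type leaves 2 (critical t 4.303). The noncentrality is 0.826 / √(2 × DE / 24), and power comes from the noncentral t distribution.

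| Assumed ICC | Noncentrality | Power, 3 df | Power, 2 df (with center type) |
|---|---|---|---|
| 0 | 2.86 | 50% | 36% |
| 0.02 | 2.59 | 43% | 32% |
| 0.05 | 2.30 | 36% | 27% |
| 0.10 | 1.97 | 28% | 21% |

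The first row does not depend on any ICC: with so few error degrees of freedom, power is far below 80% even when mothers are uncorrelated.

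**5. Would more mothers in the same centers help?** Ignoring the loss of degrees of freedom, two centers per arm need m = 24(1 − ρ) / (2 − 24ρ) mothers per center. At ρ = 0.05 this is 22.8 / 0.8 = 28.5, or 57 evaluable per arm. At ρ of 2/24 = 0.083 or above, no number of mothers is enough. The constraint is the number of centers.

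**The case against.** The strongest replies concern size and mechanism, not the mismatch itself.

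- **The mechanism is not documented.** A reader might infer that mothers in a center share sessions, staff or a neighbourhood. The article does not say so. The program is still to be designed in the second phase, and its delivery format is not given. Correlation within a center is therefore a possibility, not a stated fact. Allocation by center is enough to make the point.
- **The figures are conditional.** The ICC is assumed, and 0.83 SD rests on the back-solve from 27. The calculation uses one post-intervention score, whereas the article collects baseline scores and plans ANCOVA. Adjusting for baseline could remove part of any stable difference between centers, which would change the residual ICC and the power. This stands, and it is why ranges are given.
- **ANCOVA might be thought to cover it.** It does not. Center is nested in arm, so a fixed center effect is confounded with the program. Only center type can be adjusted for in that way.
- **The power figures are for center means.** A random-effects model may do somewhat better. An approximation that pools to mother level when the center variance is estimated at zero gave about 51-55% at ICC 0 and 44-48% at ICC 0.02. That is still well short of 80%.

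**Conclusion.** The concern holds. Allocation is by center, while the sample size and the listed tests assume independent mothers, so the stated power and confidence do not describe this design. Under the assumptions above (24 evaluable per arm, 12 per center, one post-intervention score), type I error over ICC 0.02 to 0.10 is about 8% to 18% for a two-group t-test and 9% to 25% for the three-arm ANOVA. Power of a center-means analysis for 0.83 SD is about 50% or 36% at ICC 0 (3 or 2 df) and falls from there.

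Two stronger readings are not supported. One is that the planned tests are known to be inflated by a given amount: without an ICC in the article, only a conditional range can be stated. The other is that the 80% claim is rescued by an ICC of zero: that is true only of the mother-level test, not of an analysis that respects the allocation.

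**What to change.** - **Sampling method:** call the design a cluster-randomised trial with two clusters per arm.
- **Data analysis:** replace the mother-level between-group tests with a model for the post-intervention score that has arm, baseline score and center type as fixed effects, center as a random effect, and small-sample degrees of freedom (Satterthwaite or Kenward-Roger). An analysis of the six center means is the simpler alternative.
- **Sample size:** state that 80% power applies only to the mother-level test with an ICC of zero. Give the power of the chosen cluster-respecting analysis over ICC 0 to 0.10, which is well below 80% throughout.
- **Reporting:** report the observed ICC and present p-values as preliminary.

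The cost is protocol wording and a mixed-model procedure in place of the listed tests, with no extra participants. The downside is wider intervals and a much less favourable stated power. These changes restate the power and do not restore it; restoring it would need more centers per arm.

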#### The implementation method

The researcher will implement the designed program after obtaining permission from ethics committee of Isfahan University of Medical Sciences and the necessary coordination with authorities of The Ministry of Health and Welfare and The Ministry of Exceptional Education. This is done by referring to the centers covered by The Ministry of Health and Welfare and secondary exceptional schools and presenting a letter of introduction to the authorities of those centers regarding research objectives. After that, the researcher will be allowed to access to phone numbers of girls in secondary educational schools and centers covered by The Ministry of Health and Welfare, and call their mothers in order to explain research objectives and invite them to participate in the research. If the mothers are willing to cooperate, and have all the inclusion criteria, they will be selected by convenience sampling method with their informed consent. Mothers’ awareness, attitude, and self-efficacy will be considered as the suggested outcomes. Before intervention, the questionnaires will be filled by mothers in each of the three groups. Furthermore, the questionnaires will be refilled by mothers immediately and 1 month after the intervention.

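### Mothers are recruited by convenience after their centers have been allocated, with no masking stated, so which mothers enter can depend on the arm

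*Protocol article*

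**What the plan says.** All references are to the third (quantitative) phase of the protocol article.

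- **Choice of centers (Sampling method).** Three rehabilitation centers and three schools are taken without randomisation. For the schools the text reads "two professional secondary schools and one pre-professional secondary school) will be selected non-randomly".
- **Allocation (Sampling method).** Software then assigns the centers: "one exceptional school and one rehabilitation center covered by The Ministry of Health and Welfare will be selected for each of the intervention group 1", and likewise for intervention group 2 and the control group. Each arm has two centers.
- **Recruitment (Sampling method).** The next sentence is "Afterwards, the mothers with inclusion criteria will be selected from each center via convenience sampling method".
- **Invitation (The implementation method).** The researcher is to be given the girls' phone numbers and will "call their mothers in order to explain research objectives and invite them to participate in the research". Entry is described as "If the mothers are willing to cooperate, and have all the inclusion criteria, they will be selected by convenience sampling method with their informed consent". The same section makes the researcher responsible for implementing the program.
- **Baseline (The implementation method).** "Before intervention, the questionnaires will be filled by mothers in each of the three groups".
- **Adjustment (Data analysis).** "ANCOVA will be used for adjusting intervening variables". The covariates are not named.

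**The concern.** Randomising centers balances, on average, the mothers who belong to those centers. It does not balance the mothers who are approached, or who agree, once the arm has been set. Two routes to imbalance are open:

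- a recruiter with free choice of whom to call, who may know the center's arm;
- mothers who accept or decline according to what they understand their center will receive.

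The outcomes are mothers' questionnaire scores for awareness, attitude and self-efficacy. Interest in the topic could plausibly affect both joining and later scores. A difference between arms at follow-up could then reflect who was enrolled rather than what the program did.

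**Working it through.** **1. Order of events.** As written: choose six centers, allocate them to arms, select mothers by convenience, take baseline, intervene. Recruitment follows allocation. The baseline questionnaires come before the intervention, but only mothers who have already been selected complete them. They can reveal some imbalance but cannot prevent it.

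**2. Protection from allocation alone.** With one school and one rehabilitation center per arm there are 3! × 3! = 36 possible allocations and two centers per arm. Protection against differences between centers is weak even before recruitment starts.

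**3. The plan's own figure.** The Sample size section reads "Sample size will be 27 participants in each group considering 95% confidence interval, 80% trial power, d = 2.9 for awareness, d = 11.3 for attitude", followed by a difference of 5 for self-efficacy and 10% loss. No SD is given, so 27 cannot be reproduced forward. Only the number of evaluable mothers is needed here: 27 × 0.9 = 24.3, taken as 24 (24/0.9 = 26.7, rounded up to 27).

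**4. Effect of an assumed recruitment shift.** The documents give no size for the shift. Suppose the mothers enrolled in one arm would score s SD higher at follow-up than those in another arm with no treatment effect at all. Compare the two arms with a two-sided 5% test, normal approximation, no covariates and no clustering.

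- Standard error in SD units: √(2/24) = 0.289.
- False-positive rate: 1 − Φ(1.96 − s/0.289) + Φ(−1.96 − s/0.289).

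| Assumed shift s (SD) | s/0.289 | False-positive rate |
|---|---|---|
| 0 | 0 | 5.0% |
| 0.1 | 0.35 | 6.4% |
| 0.2 | 0.69 | 10.7% |
| 0.3 | 1.04 | 18.0% |
| 0.4 | 1.39 | 28.3% |
| 0.5 | 1.73 | 41.0% |

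**5. What baseline adjustment does.** Assume s = 0.3, a baseline-outcome correlation of 0.5 and equal SDs at both times, so that the residual SD is √(1 − 0.5²) = 0.866.

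- Shift fully present in the baseline score: ANCOVA leaves 0.3 − 0.5 × 0.3 = 0.15 SD. In residual units this is 0.15/0.866 = 0.173, and the formula in step 4 gives about 9%.
- Shift absent from the baseline score (for example, readiness to respond to follow-up): ANCOVA leaves all of the 0.3 SD. In residual units this is 0.3/0.866 = 0.346, which gives about 22%.

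Adjustment helps in the first case and not in the second. Both figures ignore the small loss of precision from baseline imbalance.

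**The case against.** The strongest reply is that the article never says the arm is known or disclosed when mothers are called. It describes a single invitation procedure for all centers, with eligibility criteria fixed in advance and informed consent. Masking of the recruiter and the wording of the call could sit in a fuller protocol. Baseline is measured in all three groups and ANCOVA is planned.

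Much of this stands and limits the point. A reader might infer four stronger things that the text does not support:

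- **That the arm is known at invitation.** This can only be inferred from the order of events, from the researcher's two roles and from the lack of any stated masking. The article also does not establish that one individual fills both roles.
- **That control mothers are offered questionnaires only.** The article does not say what the control group receives, so different reasons for accepting are a possibility and not a fact.
- **That the order of recruitment destroys the protection of randomisation.** With two centers per arm there was little to lose, and reordering would leave that weakness in place.
- **That the bias can be stated as a fixed share of the planned effect.** No standardised effect is given. Solving back from 24 per arm at 80% power gives 0.81 SD for a two-sided 5% test, 0.72 for one-sided 5% and 0.93 for Bonferroni over three outcomes. A 0.3 SD shift is then 37%, 42% or 32% of it. For self-efficacy, 5/0.81 implies an SD of about 6.2, above the largest possible on the stated 0 to 10 scale (5 × √(24/23) = 5.1). The benchmark is not reliable.

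The reply does not remove the stated sequence or the convenience selection. Both are written into the plan and are not details left for another document. A masked caller would close one route, but free choice of mothers after allocation would remain.

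**Conclusion.** The plan as written permits recruitment bias: centers are allocated first, mothers are then chosen by convenience, and no masking is stated. Whether bias would occur, and in which direction, cannot be read from the documents.

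The 6% to 41% range for shifts of 0.1 to 0.5 SD is an illustration. It rests on an assumed shift, no treatment effect, 24 evaluable mothers per arm, and an unadjusted test that ignores clustering. It does not estimate this trial's error rate. The planned baseline measurement and ANCOVA reduce the problem only as far as the imbalance shows in the measured covariates. This should be changed, because the protection is cheap and cannot be recovered at the analysis stage.

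**What to change.** **Preferred: recruit before allocating.**

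1. In all six centers, list the eligible mothers from the phone lists the researcher plans to obtain.
2. Invite all of them, or invite them in random list order, using one standard script.
3. Obtain consent and complete the baseline questionnaires.
4. Only then run the allocation software and disclose the arm.

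An equal split, which the article does not state, would mean 3 × 27 / 6 = 13.5 mothers per center. The number of eligible mothers per center is not given, so this should be checked first.

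**Cost.** Protocol wording, and a delay because no center can start until all six have finished baseline.

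**If the order cannot be changed.** Replace convenience selection with inviting every eligible mother, or a random order, at each center. Use the same arm-neutral script throughout, and report the numbers approached, eligible and consenting by arm. This narrows the recruiter's discretion and makes differential acceptance visible, but it does not prevent it.

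Neither option addresses having only two centers per arm.
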